## **2. Background**

### **Problem**

The prevalence of the chronic disease overweight is around 35% and of obesity around 11% with similar numbers for Germany with 37 and 16%. The prevalence of this epidemic disease is increasing worldwide with the consequent quantities like impairment of well-being, quality of life, severe concomitant diseases, early retirement and increased mortality. This contrasts to the decreasing prevalence of other diseases. Current evidence-based interventional studies do not lead to the desired persistent weight loss.

### **Epidemiology and definition Epidemiologie und Definition**

In 2015, 1.5 billion people will be overweight or obese. Overweight and obesity are associated with increased mortality. This disease is one of the five risk factors that most often account for worldwide mortality with estimated 3.4 billion death per year (August 2014).

Overweight and obesity most often are defined over the so-called body-mass index (BMI). Other measures are waste circumference or the relation of waist / hip ratio to identify abdominal fat. Abdominal fat in man and serves to identify increased health risks. Prevalence of overweight (BMI 25 to 30) in the German population lives around 37% (worldwide 35%) and of obesity (BMI >30) are around 16%, (worldwide 11%). Increasing over the last years. With increasing age, prevalence increases in both genders, with around 50% of men and 33% of women aged of 55 to 60 overweight or obese. In Germany, 40 million people are overweight. 35% (32 million) and 13% (12 million) of the working population are overweight or obese. In the working population (aged 18 to 40 and 65 years), 11% (39 more than non-obese) or 22% (18% more than non-obese) will call sick. As the WHO noted, these data warrant the considerable need for action and therapy to stop the increasing prevalence.

### **Direct and indirect costs**

To be able to calculate the costs and to compare diseases, two key figure are calculated, derived from age of the patient at onset of disease, life expectancy of the person and extend of disability. Following the Global Burden of Disease (GBD), quality of life is defined as negative index of disability defining "Disability-Adjusted Life Year" (DALY). In contrast to other diseases (cardiovascular new plater) costs have been increasing for overweight and obesity worldwide by more than 30%. High BMI is a leading risk factor (6/25) for DALYs worldwide. All components of diet and physical inactivity that lead to overweight and obesity, make 10.2% of DALYs.

In addition to the direct costs that result from a disease (medical treatment, prevention, rehabilitation or nursing activities), considerable indirect costs result for the community. These arise from reduced working ability and early retirement. Patients with obesity have additional costs, that result from stigmatisation with consequent academic or professional achievements, including exclusion from better paying jobs.

## **Evidence-based intervention programs**

Overweight and obesity can be prevented through environmental and community measurements. For weight reduction and to stabilise reduced weight, basic measures like teachings, behavioural changes, physical activity and healthy eating with a deficit in energy form the basis in evidence-based weight reduction programs. The advantages of weight reduction, even by 10%, regarding mortality, general health and obesity-associated diseases are well documented. Weight reductions result in improvements of diabetes mellitus 2, hyperlipidaemia, arterial hypertension, cardiovascular risk profile and ovary function, furthermore of reduced breathlessness, improvement of quality of sleep, sleep apnoea, back and joined pain, as well as osteoarthritis and psychosocial components.

Regardless of the composition of the diet a daily deficit of energy of around 500 cal per day results in a weight reduction of around 1.5 to 4.5 kg over a longer period. Cost-effective is defined as measures is for weight reduction that costs less than US\$50,000 / DALY. This is the case for all state and societal programs as well as for most diets and behavioural changes.

The high percentage of quitters (45%) of programs and the so-called yo-yo effect with weight regain after nearly all programs are highly problematic. Current prevention therapies are characterised by a disproportional weight regain after interventions. This is especially the case for elderly patients that are not used to weight reduction programs including sufficient physical activity. This leads to constant weight gain with increasing age of the community and the individual.

Factors that influence the quantity of food include the quantity and variety of the food offered, visual and anticipatory stimuli and other behavioural patterns as well as satiety. Satiety is a complex process that is mediated by diverse short, middle and long acting mediators in the hypothalamus. Different brain areas integrate these complex neuronal and hormonal signals and thus influence food intake and other behavioural patterns or the emotional state.

### **Surplus studies being carried out and if yes, what was the result?**

No/not applicable

### **3. Hypothesis**

The aim is to test the main hypothesis that using the Genustrainers will lead to a persistent weight reduction.

#### **3.1. What is expected?**

From this analysis of the first volunteers the hypothesis shall be tested that

- there was a continuous increase of weight and of the visceral fat over the last 10 years related to the baseline weight when they splints were first used

- there will be a weight reduction and reduction of the visceral fat and now weight regain, even after stopping using the splints.

### 3.2. Aim of the study

Primarily the efficacy of the splints shall be proven. The primary endpoint is weight reduction after using the splints. Secondary endpoints regarding mode of action, safety and benefit shall be analysed, if the existing documentation and is sufficient.

Hereafter, the splints shall be standardised regarding the construction and further specified. This will form the basis for the development and certification of the medical device (MD) risk class I and consequent testing in a clinical trial.

It will be the aim of this retrospective analysis of the current observational study to obtain data so that a study protocol can be derived from this including a proof of mechanism for a then certified MD.

A large-scale prospective randomised controlled trial shall be planned to prove the main hypothesis and further to be identified secondary hypotheses to test the splints as medical device.

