### **5. Study design**

This is a retrospective analysis to be carried out after obtaining written informed consent of the volunteers that their data shall be used for scientific research (see appendix).

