## **6. Number of patients / volunteers**

Five volunteers (+ the inventor) have used the MD. Data from these volunteers shall be analysed.

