## **7. Statistics**

This is a retrospective analysis. Most likely, data of some variables will be missing. Data from weight courses/visceral fat from the last 10 years shall be analysed. Most likely only weight courses might be documented. This will only have been done according to clinical necessity. There will be no standardisation regarding time points.

All continuous variables shall be checked for normal distribution with the Kolmogorov-Smirnov test. Data shall be expressed as mean expressed as mean  $\pm$  standard deviation. Normally distributed variables shall be analysed with the two-sided t-test. Not normally distributed variables shall be analysed with the Mann-Whitney-U Test. Comparison of categorical variables shall be generated with the Pearson  $\chi^2$ -test and the Fishers exact test. The linear regression analysis shall be used to identify independent predictors for weight reduction in the follow-up period. Is not expected that these tests shall be used regarding the small number of volunteers. Statistical significance shall be assumed if a null hypothesis can be rejected at  $p \leq 0.05$ . All statistical analysis shall be performed with SPSS 20 ®.

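### Section 3.2 sets out to prove efficacy from five or six uncontrolled users, and Section 7 contradicts itself on whether any inference will be made

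*Protocol*

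**What the plan says.** Protocol Section 3.2 (Aim of the study) opens with "Primarily the efficacy of the splints shall be proven" and continues "The primary endpoint is weight reduction after using the splints". Further on, the same section describes the work as a way to obtain data from which a study protocol can be written, and adds: "A large-scale prospective randomised controlled trial shall be planned to prove the main hypothesis". Sections 3 and 3.1 speak of testing hypotheses about persistent weight reduction.

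Section 5 gives the design: "This is a retrospective analysis to be carried out after obtaining written informed consent of the volunteers". Section 6 gives the size: "Five volunteers (+ the inventor) have used the MD", followed by "Data from these volunteers shall be analysed". Whether the inventor counts among those analysed is not said. No control group is described anywhere in the protocol.

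Section 7 lists a Kolmogorov-Smirnov check, a two-sided t-test, Mann-Whitney, chi-square and Fisher's exact tests. It then states: "The linear regression analysis shall be used to identify independent predictors for weight reduction in the follow-up period". The next sentence reads: "Is not expected that these tests shall be used regarding the small number of volunteers". The one after that sets the significance threshold at p ≤ 0.05. Apart from mean and standard deviation, no analysis is named to take the place of the tests.

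**The concern.** There are two faults in the stated text.

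First, the primary aim is a conclusion that the design cannot support. Section 4 itself records changes in physical activity, eating behaviour and medication during follow-up. Each is a rival explanation for weight loss, and without a comparator none can be separated from an effect of the device. Section 8 also requires at least two documented visits after receiving the device, so people who gave up early can fall outside the analysis. A small p-value would not cure either problem.

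Second, Section 7 does not settle whether inference will be made. The regression is prescribed, then not expected, and the significance rule remains in force with no test expected to use it.

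Section 3.2 makes this work the basis for device development, certification and the randomised trial. An unsupported efficacy statement or a chance predictor could therefore carry forward into those steps.

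**Working it through.** The protocol gives no power, effect size or standard deviation, so there is no figure of its own to reproduce. The check is what the named methods can deliver at the stated size.

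**Inputs.** n = 5 (volunteers only) or n = 6 (with the inventor), from Section 6. Two-sided level 0.05 and the list of methods, from Section 7. The number of predictors k is not stated, so values of k below are assumptions.

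**Regression: degrees of freedom.** Residual df = n − 1 − k.
- n = 5: zero at k = 4.
- n = 6: zero at k = 5.

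At that point the model fits the data exactly, whatever the data are.

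**Regression: one predictor.** The smallest significant correlation is |r| = t / √(t² + n − 2), with t the 97.5% point on n − 2 df.
- n = 5: t = 3.182, so |r| = 3.182 / √(10.13 + 3) = 0.88.
- n = 6: t = 2.776, so |r| = 2.776 / √(7.71 + 4) = 0.81.

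**Regression: fit from noise.** With no true effect, expected R² = k / (n − 1). For an assumed k = 3 this is 3/5 = 0.60 at n = 6 and 3/4 = 0.75 at n = 5.

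**Group tests.** Section 7 names no groups. For any split of 5 or 6 people into two groups, the smallest attainable two-sided exact p is:

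| Split | Mann-Whitney | Fisher's exact |
|---|---|---|
| 1 v 4 | 0.40 | 0.20 |
| 2 v 3 | 0.20 | 0.10 |
| 1 v 5 | 0.33 | 0.167 |
| 2 v 4 | 0.133 | 0.067 |
| 3 v 3 | 0.10 | 0.10 |

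Neither exact test can reach 0.05.

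**Before-after change.** Section 7 does not say whether the t-test is paired. If it is, the 95% CI half-width is t / √n in units of the SD of change: 2.776 / √5 = 1.24 (n = 5) and 2.571 / √6 = 1.05 (n = 6). A large change could reach significance, but it would still have no comparator.

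**Planning values.** For normal data, the 95% limits of an SD are the estimate times √(df / χ²).
- n = 6, df = 5: √(5 / 12.83) = 0.62 and √(5 / 0.831) = 2.45.
- n = 5, df = 4: √(4 / 11.14) = 0.60 and √(4 / 0.484) = 2.87.

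A sample size is proportional to SD², so the uncertainty factor is 5 / 12.83 = 0.39 to 5 / 0.831 = 6.0 at n = 6, and 4 / 11.14 = 0.36 to 4 / 0.484 = 8.3 at n = 5.

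**The texts side by side.** In Section 3.2, proof is both the primary aim of this review and the task of a later randomised trial. In Section 7, three consecutive sentences prescribe the regression, say the tests are not expected to be used, and set the rule for judging them.

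**The case against.** The best defence is that the authors already know this is descriptive. Section 3.2 says the purpose is to obtain data for a later protocol and reserves proof for a randomised trial. Sections 3 and 3.1 speak of testing, not proving. The English is visibly a rough translation, so the verb in the aim may be looser than intended. The disclaimer in Section 7 directly follows the regression sentence and on a natural reading covers it. The study is a record review of existing users and changes nobody's treatment.

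Much of this stands, and it lowers the severity. It does not remove the fault. If the work is descriptive, then the aim of proof, the prescribed regression and the significance rule contradict it. The disclaimer reaches only the tests and leaves the aim and the threshold standing.

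Two stronger readings are tempting, and the protocol does not support them. A reader might infer that p-values will be shown only if favourable. The stated reason for not testing is the small number of volunteers, which is fixed in advance and does not depend on results; selective reporting would be speculation about conduct. A reader might also take the long variable list in Section 4 as the set to be screened for predictors and calculate a false-positive rate from it. Section 7 never says which variables enter the regression or that they are tested one by one. The list also contains dates, free-text items and overlapping measures such as weight, height and BMI.

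**Conclusion.** The point holds as a conflict in the stated text together with an aim beyond the reach of the design. Five or six users reviewed retrospectively without a comparator cannot prove efficacy, whichever test is applied. This conclusion does not depend on any of the calculated figures.

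The figures show that the regression cannot identify independent predictors at this size, and that even the planning use is limited: the factor of 0.39 to 6.0 on a sample size assumes normally distributed changes and all six users. The R-squared example assumes three predictors, a number the protocol does not give. The analysed number could be smaller still if the criteria in Section 8 remove anyone.

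This should be fixed, but it is not a fatal flaw: the remedy is wording, and the protocol already contains the descriptive purpose that ought to be the stated aim.

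**What to change.** **Section 3.2, with Sections 3 and 3.1 aligned.** State the aim as describing the weight course before, during and after use of the device and obtaining planning values for the randomised trial. Say that no conclusion on efficacy will be drawn.

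**Section 7.** Delete the regression, the group-comparison tests and the p ≤ 0.05 rule. Commit to individual listings and plots of weight over time. Add the within-person change from time point 0 to one point named in advance, for example the last documented visit, with each person's follow-up duration shown. The point has to be named because Section 7 says time points are not standardised. Report the mean and SD of that change with 95% CIs, labelled as descriptive and for planning only; otherwise an interval that excludes zero brings the deleted significance rule back in another form.

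**Section 6.** State whether the inventor is analysed. If so, show results with and without the inventor.

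**Cost.** Text changes in five sections and no new data. The sponsor gives up an efficacy claim and a predictor analysis that the design cannot support. If the last documented visit is chosen, follow-up will differ between people, so the SD of change will mix durations and should be used with that caution in planning.

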### 4. Targets

Following the main hypothesis data shall be analysed regarding the following influencing and target variables:

#### Baseline values:

- age (in years) and time point 0
- gender
- date of time point 0 and of the earliest documented weight
- weight and waist circumference at time point 0
- height at time point 0
- BMI at time point 0
- categories: BMI > 25, BMI > 30, BMI > 35 .0
- duration of previous attempts to reduce weight
- development of weight and waist circumference over the last years
- number of previous attempts to lose weight
- type of weight reduction programs
- change of medication and inclusion (one month follow-up periods)
- Concomitant diseases
- metabolic syndromes (yes / no)
- Diabetes mellitus (y/n)
- Duration Diabetes mellitus (only in DM patients)
- family history for premature cardiovascular events; m < 55 years , w < 65 years, (y/n)
- current smokers , (y/n)
- hyperlipoproteinaemia (diabetes LDL > 70 mg / dl, non-diabetes> 100 mg /dl OR statin therapy), (y/n)
- art. Hypertension, (y/n)
- number of cardiovascular risk factors (including: family history; m < 55 years , w < 65 years , smoking , hyperlipoproteinaemia (diabetes LDL > 70 mg / dl, non-diabetes> 100 mg /dl OR statin therapy), art. hypertension , Diabetes mellitus)

- orthopaedic problems (y/n)  
type of orthopaedic problem
- social economic status, training, income (rough estimation), status employee, retired

#### Target variables

- **weight, BMI and waist circumference after using the MD**
- duration of follow-up (in month all years)
- number of follow-up visits
- date of last follow-up visit
  
- Concurrent medication
- change of medication during follow-up (y/n), which?
  
- Laboratory findings:
  - HLP, HBA1C, hs-CRP, BB,
- Sports or physical activity
- adherence of using the MD
- subjective details regarding the MD
- change of eating behaviour
- psychologic statement of the personnel of the medical practice of [name]
- change of quality of life and physical performance

Time point 0 is the visit at which the patient decided to use the MD.

### **5. Study design**

This is a retrospective analysis to be carried out after obtaining written informed consent of the volunteers that their data shall be used for scientific research (see appendix).

#### Choice of data

See Number 4.

#### Origin of data

All data shall be extracted from patients records by two independent nurses or the lead investigator. In doubt there will be a consultation and consensus building. In case that one of the volunteers is not a patient of the medical Praxis, data will be obtained via telephone and /other rackets provided by the patient will be reviewed.

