#### Acquisition of data

Data will be acquired in electronic database and pseudomised. Thereafter, data will be analysed statistically with SPSS. Prior to analysis they will be examined for completeness, accuracy and credibility.

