## **8. Inclusion and exclusion criteria**

### **Inclusion criteria**

1. age: 18 to 95 years
2. gender male and female
3. ability to consent
4. written informed consent
5. exploit of the established evidenced-based options for weight reduction
6. receiving an MD
7. at least two documented visits after receiving the MD

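### Section 5 permits extraction by the lead investigator alone and telephone-reported data for non-patients, and nothing requires the primary-endpoint weights to be documented

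*Protocol*

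**What the plan says.** The primary endpoint is in Section 3.2: "The primary endpoint is weight reduction after using the splints". Section 4 defines time point 0 as the visit at which the patient decided to use the device, and lists weight at that point among the baseline values.

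Section 5, Origin of data, sets the source and the extractor. The default is the patient record: "All data shall be extracted from patients records by two independent nurses or the lead investigator". The next sentence adds: "In doubt there will be a consultation and consensus building". For a volunteer from outside the practice there is a second route: "In case that one of the volunteers is not a patient of the medical Praxis, data will be obtained via telephone". That sentence goes on to say that "rackets provided by the patient will be reviewed"; the garbled word probably means records.

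Two other provisions bear on data quality. Section 5, Acquisition of data, says of the data: "Prior to analysis they will be examined for completeness, accuracy and credibility". Inclusion criterion 7 in Section 8 requires "at least two documented visits after receiving the MD". Section 7 concedes that weights were recorded only when clinically needed and adds: "There will be no standardisation regarding time points". Section 6 gives the size of the group: five volunteers, plus the inventor.

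**The concern.** There are two weaknesses, and both reach the primary endpoint.

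The first is the *or* in the extraction rule. Independent extraction by two people protects against transcription error and against selective reading, because two readings can be compared. The rule offers this safeguard and then makes it optional. When the lead investigator extracts alone there is no second reading, so a disagreement cannot come to light. Weights were recorded irregularly, so deciding which entry counts involves judgement.

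The second is the telephone route. No provision confines it to variables that only the volunteer can report, and none requires a documented weight before a value enters the primary endpoint. Because the analysis is retrospective, a weight reported by telephone would be given after the volunteer knows how things turned out.

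With five or six people, one wrong value moves the mean noticeably. Section 3.2 intends these data to inform the protocol of a later study, so an error here could carry forward.

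**Working it through.** The protocol states no figure on this point, so there is none to reproduce. The check is a reading of the provisions together, followed by a simple illustration of scale.

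**Which provision protects which weight**

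| Provision | Weight at time point 0 | Weights after the device |
|---|---|---|
| Extraction from records (Section 5) | Default source, but with an exception for non-patients | Same |
| Two independent nurses (Section 5) | Optional, because the lead investigator is an alternative | Same |
| Consultation in case of doubt (Section 5) | Only if someone notices a doubt | Same |
| Patient-supplied material (Section 5) | Reviewed, but not a condition for using a telephone value | Same |
| Check before analysis (Section 5) | Applies, but no method is given; it cannot verify a reported weight that has no source record | Same |
| Inclusion criterion 7 (Section 8) | Not covered: it concerns visits after receipt | Two documented visits, but not stated that weight was measured at them |

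Every row leaves a way for an undocumented or singly extracted weight to enter the primary change. The gap is wider at time point 0, where criterion 7 gives no help.

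**Scale**

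Inputs: n = 5 volunteers, or n = 6 with the inventor (Section 6). The error b in one person's weight change is an assumption, taken as 2 to 5 kg, because the documents give no figure for recall or extraction error.

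A person's change is the follow-up weight minus the weight at time point 0. An error in either one passes kilogram for kilogram into the change. If one person's change is wrong by b and the others are right:

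shift of the mean change = b / n

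- n = 5: 2/5 = 0.4 kg; 5/5 = 1.0 kg
- n = 6: 2/6 = 0.33 kg; 5/6 = 0.83 kg

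The formula gives the size of the shift only. Its direction depends on which weight is wrong and in which sense, and the documents do not settle that.

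**The case against.** The case on the other side is substantial.

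- **The telephone route is conditional.** It applies only if a volunteer is not a patient of the practice, and the protocol does not say that any of them is. A reader might infer that the primary weights do mix measured and recalled values. The text supports only that they may.
- **The telephone is not the only source.** Patient-supplied material is reviewed too. This lowers the risk, but it is not made a condition for using a weight.
- **Criterion 7 is not contradicted.** A reader might see a conflict between telephone data and documented visits. A non-patient can have visits documented elsewhere, so the two provisions are compatible. The criterion helps for weights after the device.
- **The 10-year history is a separate matter.** Distant weights are the hardest to recall, but they serve the hypothesis in Section 3.1 about weight gain before the device. They are not the primary change.
- **Knowledge of the hypothesis is not documented for the nurses.** It is a fair inference for the lead investigator, but the protocol is silent on what the nurses know. Everyone used the device, so there is no allocation to mask, and two nurses would not make extraction blind. What they add is an independent second reading.
- **No expected effect is available for comparison.** The protocol states none for the splints. Its figure of 1.5 to 4.5 kg in Section 2 concerns a dietary energy deficit, so it would be wrong to express the shift as a share of the expected effect. A bias towards greater weight loss is likewise not shown.
- **Some detail may belong elsewhere.** Consensus in case of doubt is not limited to the nurses, and source flags or listings are often left to an analysis or data-management plan. That answers the absence of a listing. It does not answer a protocol that itself fixes who extracts and from what source, and does so in a way that allows single extraction and unverified weights.

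**Conclusion.** The point holds in a limited form. As written, Section 5 permits the lead investigator to extract alone. For a non-patient it permits telephone-reported data without requiring that the weights behind the primary endpoint be documented. Criterion 7 and the data check narrow the exposure after the device, but leave the weight at time point 0 open and do not establish that weight was measured. The primary change may therefore contain unverified or singly chosen values; the documents do not show that it does.

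The possible shift in the mean, 0.4 to 1.0 kg with five people or 0.33 to 0.83 kg with six, rests on two assumptions: that exactly one person's change is wrong, and that the error is 2 to 5 kg. It shows how sensitive a group this small is and is not an estimate of actual bias. The rule should be tightened before the data are extracted.

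**What to change.** Make two changes in Section 5, Origin of data.

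1. Have the two nurses already named extract the weights independently for every volunteer, and limit the lead investigator to resolving disagreements.
2. Base the primary weight change on dated weights documented in the practice chart or in a record supplied by the patient, at time point 0 and at follow-up alike. Flag any weight known only by telephone and show it in a separate listing or sensitivity summary.

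The telephone can stay for variables that depend on the volunteer's own account, such as adherence, eating behaviour and quality of life.

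The cost is a change of wording, one source field in the database and a little more extraction work for five or six people. The real downside is that a volunteer without documented weights would drop out of the primary summary and appear only in the sensitivity listing, which matters in a group this small.
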